### Who will take informed consent? {26a}

#### Informed consent procedures

Informed consent for the trial will be obtained by study field workers and nurses with appropriate English and local language skills. However, in addition, all participants/parents will speak to the study doctor before final agreement to ensure any outstanding questions, particularly anything of a medical nature have been fully and accurately addressed.

Consent can only be obtained from adults who are at least 18 years old. Therefore, if both parents of a toddler or infant are under 18 years of age, the child cannot be enrolled in the study.

Informed consent is the process of ensuring that potential study participants/the parents of potential study participants understand the purpose of the study, what participation will involve, the potential risks and benefits of participation, their rights and commitments as study participants and all other information set out in the informed consent document (ICD) (as per ICH-GCP E6 (R2) section 4.8.10). Prior to any study-specific procedures taking place, signed/thumb-printed, timed and dated, written informed consent for trial participation must be obtained using an ICD approved by the Gambia Government/MRC Joint Ethics Committee and the LSHTM Research Ethics Committee. A certified copy of the completed ICD will be provided to the participant/parent at the end of this process. The outcome of the informed consent process (i.e. consented/did not consent) will also be captured in the consent log for the trial.

The entire informed consent process may be undertaken either in English or in one of several local languages for participants who are not sufficiently English literate.

Written informed consent will only routinely be obtained once at the start of the trial irrespective of the interval between consent and screening (or re-screening if applicable). However, a participant/parent will be given the chance to ask any questions at each study visit and ongoing willingness to participate will be confirmed and documented. If new information becomes available during the course of the trial which may be relevant to a participant’s willingness to participate (e.g. significant new information regarding the safety profile of the MRV-MNP, etc.) written informed consent will be repeated using the processes outlined below using an updated ethically approved ICD or ICD addendum as appropriate.

#### Overview of informed consent procedures

Whether undertaken in English or a local language, the ICD will be reviewed line-by-line with the participant/parent by the person undertaking the consent process ensuring all details are covered and understood. Self-reading alone is not considered to be sufficient. During this review, chances to ask questions and seek clarification will be given by the person taking consent. After this review, all participants/parents will be seen by a study clinician who will give them a further chance to ask questions and will also clarify any questions, particularly of a medical nature, that the person taking consent was unable to address. In addition, prior to signing/thumb-printing the ICD, the participant/parent must successfully complete an ‘Assessment of Understanding’ undertaken by the study clinician in the presence of a different member of the trial team to the individual undertaking the rest of the informed consent process. This series of questions, approved by the appropriate ethics committee and related to the content of the ICD, aims to confirm key information regarding the trial has been understood. The outcome of the assessment (enrol/repeat consent process/do not enrol) will be handled based on the study-specific procedure covering informed consent for the trial.

#### Consent by participants/parents who are English literate

When the participant/parent providing informed consent is literate in English, an impartial witness must not be present during the informed consent discussions and signature process.

English literacy will be confirmed by the individual undertaking consent. The potential participant/parent will be asked to read one or two paragraphs of the ICD and should then be asked to explain the meaning in their own words. If English literacy is confirmed, the entire informed consent process must take place in English. No local language should be used, e.g. to explain further difficult concepts. Therefore, if there is any doubt regarding the person’s level of English literacy, consent should take place in the most appropriate local language (this does not preclude the use of English but ensures that an impartial witness is present who will attest to the accuracy and completeness of the information provided).

An English-literate participant/parent will sign the ICD for themselves.

#### Consent by participants/parents who are not English literate

As the local languages in The Gambia are spoken and not widely written, the ICD is provided in written form in English only and translated directly into relevant local languages by the person undertaking consent. Previous attempts to translate and back-translate ICD into local languages have resulted in loss of meaning and thus are not used. A recording of the ICD in local languages is made prior to the initiation of consent procedures to ensure language use is consistent, accurate and agreed upon by all those taking consent. The accuracy of the agreed translation is confirmed by an individual external to the trial team, and this is documented.

When a participant/parent is not sufficiently literate in English, an impartial witness must be present throughout the informed consent discussions, assessment of understanding and signature process. Both the impartial witness and the individual taking consent must be fluent in English and in the local language used and this fluency must be documented in their curriculum vitae. The language in which informed consent is undertaken should generally be the language in which the individual being consented is most fluent (which may not be the tribe to which they belong). Impartial witnesses are not part of the clinical trial team but instead are recommended by the local community (for example, by the Alkalo [village head]) and attend the trial site on a rotational basis to ensure they remain independent.

A non-English literate participant may thumb-print or sign the ICD according to their preference. The impartial witness will time and date the signature/thumbprint on behalf of the participant.

At the end of the process, the impartial witness will also sign. In signing, they are attesting to the fact that all the information in the ICD has been given accurately and appears to have been understood by the person providing consent, that an opportunity has been given to ask questions and that these questions have been answered to the apparent satisfaction of the person providing consent and that consent is being given freely. This is the only role of the impartial witness. They should not in any way influence the decision-making of the participant/parent.

#### Consent by guardians

Consent can only be provided by a guardian rather than a biological parent if both biological parents have passed away or both parents are out of the country for a prolonged period and another adult is therefore bringing up the child. Guardians cannot consent if the parent is in another part of The Gambia or is out of the country only short term. As guardianship is very rarely transferred legally in The Gambia, anybody meeting the described criteria must sign a guardianship statement at the first visit, before informed consent procedures are undertaken. Biological parenthood will be established based on verbal report and will be documented. An additional source for this information is not required. The only exception to the above would be in the circumstances in which guardianship had been legally transferred to another adult and an official document was available to confirm this. A certified copy of such a legal document would be made under these circumstances. ‘Parent’ is used throughout the protocol but includes guardian under the conditions described.

#### Additional consent provisions for collection and use of participant data and biological specimens {26b}

As part of the process, informed consent will be sought for the future use of any remaining samples and associated data for ethically approved research which is expected to benefit the people of The Gambia. Such future use could include genetic testing. Failure to provide such informed consent will not preclude enrolment in the trial itself.

## Interventions

### Explanation for the choice of comparators {6b}

The trial will compare the administration of the MRV by MNP to the administration of the same vaccine by SC injection. In both cases, the MRV is manufactured by the Serum Institute of India Pvt. Ltd. The vaccine is licensed for SC injection under the Central Drugs Standard Control Organization of India and pre-qualified by the WHO for supply through UNICEF and other UN agencies. The vaccine meets the requirements of the WHO when tested by the methods outlined in WHO TRS 840 (1994).

To minimize the risk of bias in the safety or other data collected, the trial is of a double-dummy design meaning that all participants receive both an MNP and a SC injection. Participants who receive the MRV via the MNP receive a SC placebo injection (0.9% (weight/volume) sodium chloride). Participants who receive the MRV via SC injection receive a PLA-MNP. Neither the participants, nor the trial staff administering the MNP and SC injections, nor any staff involved in safety or other data collection will therefore be aware of the group to which an individual belongs. Given the importance of ensuring the safety data are robust, as this is the first use of the MRV-MNP in humans, this approach was felt to be warranted. As the MNP application is expected to cause little or no discomfort, the approach was also judged to be warranted in toddlers and infants who will therefore only get the one SC injection as per the normal EPI schedule.

### Intervention description {11a}

Both the SC injection (0.5 mL) and the MNP contain not less than 1000 CCID50 of the attenuated Edmonston-Zagreb measles and Wistar RA 27/3 rubella viruses.

The MNP are manufactured by Micron Biomedical, Inc. The MRV is incorporated into microneedles that dissolve and deliver the vaccine into the skin on application. The excipients from which the microneedles are made are of pharmaceutical-grade and are found on the United States (US) Food and Drug Administration (FDA)’s Inactive Ingredient Database for Approved Drug Products. The placebo microneedles contain the same excipients but do not include the measles and rubella virus antigens. The MRV-MNP and the PLA-MNP are visually indistinguishable in appearance and will be applied to the dorsal aspect of the wrist.

The MRV for SC injection is lyophilized and reconstituted with the sterile water diluent immediately before administration. The 0.9% (weight/volume) sodium chloride is presented in a sterile ampoule. The SC injections will generally be administered to the lateral aspect of the deltoid area in adults and to the lateral aspect of the thigh in toddlers and infants. All SC injections will be administered with a 0.5-mL fixed-dose, auto-disable syringe and 25-mm 23G needle.

The MNP will be applied for 5 min and removed before the SC injection is administered.

### Criteria for discontinuing or modifying allocated interventions {11b}

All participants receive a single MNP and a single SC injection at visit 1. If a participant was to have a severe, early allergic/anaphylactic reaction to the MNP (applied first), the SC injection would not be administered. In addition, a participant/parent can withdraw at any time and thus could withdraw having received the MNP and before the SC injection.

### Strategies to improve adherence to interventions {11c}

Both the MNP and SC injection will be administered at a single timepoint by study staff therefore adherence monitoring is not relevant. All participants will be monitored by staff while the MNP is in place to ensure it is not disrupted.

### Relevant concomitant care permitted or prohibited during the trial {11d}

Participants should not receive non-study vaccines during the trial, apart from any non-MRV administered as part of catch-up/national campaigns by the Ministry of Health. If an MRV SIA (generally targeting under 5-year-old children) occurs during the trial, the parents of participants will be asked not to have their child vaccinated during the campaign. All toddlers and infants will receive an additional SC dose of an MRV at the end of their participation in the trial. Other EPI vaccines due at 9 months in infants (yellow fever and bivalent oral poliovirus vaccine (bOPV) and at 15 to 18 months in toddlers (diphtheria, tetanus and pertussis and bOPV) will be administered at the day 42 post-vaccination visit.

Participants expecting to require immunosuppressant medication, intravenous immunoglobulins or blood products during their participation in the trial will be ineligible to be enrolled. However, no medication or treatment that is subsequently clinically indicated during the trial will be forbidden. Under such circumstances, safety follow-up will continue as planned to the degree possible. The decision to include the immunogenicity data for any such participants in the final analysis will be agreed between the sponsor and investigator prior to unblinding. Topical glucocorticoids for skin lightening and traditional and local herbal medications, including those applied topically, are not permitted during the trial.

### Provisions for post-trial care {30}

For health complaints which are judged to be unrelated to vaccination or trial participation — including conditions identified at screening, participants will receive initial care according to current established good medical practice within The Gambia. According to the nature of the complaint, such care (including, as appropriate, any additional investigations or treatment required) may be provided at the clinical trial site by study clinicians, within the MRCG CSD, or within government, non-governmental agency or private health care facilities. Decisions regarding the most appropriate location for treatment will be made on a case-by-case basis, involving the principal investigator and other senior clinicians in The Gambia when necessary. Such decisions will aim to ensure the care of the participant is in line with good medical practice based on current availability in The Gambia. For unrelated complaints, the trial team aim to ensure acute conditions are investigated and treated appropriately and that care for any chronic conditions is established. Long-term care for chronic conditions will not be provided by the trial team.

Any health complaints judged to be related to vaccination or trial participation will be investigated and managed in the most appropriate health care facility which may include health care facilities outside The Gambia. Financial cover to ensure such care, including for emergency evacuation, will be provided through the sponsor’s clinical trial insurance.

### Outcomes {12}

#### Study outcome measures

#### Primary — safety and tolerability

The number, severity and relatedness of solicited local and systemic AEs collected on the day of study product administration and daily until day 13 following study product administrationThe number, severity and relatedness of unsolicited AE and SAE from the day of study product administration until day 180 following study product administrationThe number, severity and relatedness of biochemical and haematological abnormalities occurring until day 14 (adult cohort only) or day 7 (toddler and infant cohorts) following study product administration

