Serious and/or severe reactions can occur following any vaccine and can be life-threatening. This trial will provide the first human data on the administration of the MRV using an MNP. While the safety data on both the vaccine itself and the MNP-based delivery method are supportive, the possibility of unpredicted reactions remains. To minimize any risk, the eligibility and screening procedures will ensure that only healthy participants are recruited. In addition, a sentinel dosing cohort will be used at the start of the trial to minimize the number of participants exposed to the intervention on a single day. Safety data including safety laboratory evaluations will be assessed in the sentinel group prior to further recruitment proceeding. In the toddler and infant cohorts, recruitment will also start slowly, with only a small number of participants being recruited each day over the first week.

Delaying the administration of the other EPI vaccines due until the day 42 visit is not associated with any substantial risk given the risks of the diseases covered by these vaccines in the indicated window is low and/or children will already have been vaccinated against these conditions (yellow fever, poliovirus type 1 and 3 and meningococcus group A, diphtheria, tetanus and pertussis).

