### Trial design {8}

This is a phase 1/2, single-centre, double-blind, double-dummy, randomized, active-controlled, age de-escalation trial.

All participants will receive either the MRV-MNP and a placebo (0.9% sodium chloride) SC injection (PLA-SC) or a placebo-microneedle patch (PLA-MNP) and MRV by the SC route (MRV-SC). Only those study staff randomizing participants and preparing the study products for administration will be aware of the group to which a participant belongs. Those administering the study products, all other trial staff collecting safety and immunogenicity endpoints, and the participants and parents will be blind.

Decision regarding age de-escalation will be based on a review of the safety data from the preceding cohort (adults for toddlers and toddlers for infants) up to day 14 post-study product administration by an independent data monitoring committee (DMC).

In all, 45 adults (18 to 40 years of age) will be randomized in a 2:1 ratio. Thus, 30 adults will receive MRV-MNP and PLA-SC and 15 adults will receive MRV-SC and PLA-MNP. A total of 120 toddlers (15 to 18 months of age) will be randomized in a 1:1 ratio. Thus, 60 toddlers will receive MRV-MNP and PLA-SC while the same number of toddlers will receive MRV-SC and PLA-MNP. A total of 120 infants (9 to 10 months) will also be randomized in a 1:1 ratio. Thus, 60 infants will receive MRV-MNP and PLA-SC while the same number of infants will receive MRV-SC and PLA-MNP.

Solicited local and systemic adverse events (AEs) will be collected daily from all participants from the day of study product administration to day 13 post-study product administration. Unsolicited AE and serious adverse events (SAEs) will be collected from the day of study product administration to day 180 post-study product administration. All participants will have laboratory investigations (human immunodeficiency virus [HIV], hepatitis B, hepatitis C, haematology and biochemistry) conducted as part of screening. Adults will have safety laboratory investigations repeated on day 7 and day 14 post-study product administration. Toddlers and infants will have safety laboratory investigations repeated on day 7 post-study product administration only. All cohorts could have further laboratory investigations undertaken as clinically indicated.

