#### Inclusion criteria

A prospective participant must meet all the following inclusion criteria to be eligible for enrolment (randomization and vaccination):

Participants must:Provide voluntary written/thumb-printed informed consent for trial participation (adult cohort)Have voluntary written/thumb-printed informed consent provided for them by a parent (toddler and infant cohort)Be between 18 and 40 years inclusive on the day of consent. They will be eligible from the day they reach 18 years of age until the day before they reach 41 years of age (adult cohort)Be between 15 and 18 months of age inclusive on the day of consent. They will be eligible from the day they reach 15 months of age until the day before they reach 19 months of age (toddler cohort)Be between 9 and 10 months of age inclusive on the day of consent. They will be eligible from the day they reach 9 months of age until the day before they reach 11 months of age (infant cohort)The identity and age of all prospective participants must be as confirmed from a suitable source document prior to informed consent. Suitable source documents include but are not limited to the birth certificate, national identification card, passport and, in toddlers and infants, the parent-held infant welfare card (IWC). Photographic identification is not consistently available and is not required. Participants/parents will be issued with a trial photographic identification card once randomization and vaccination have taken place (visit 1).Be judged to be able to comprehend and comply with study requirements and procedures and must be willing and able to return for all scheduled follow-up visits (adult cohort)Have a parent who is judged to be able to comprehend and comply with study requirement and procedures and is willing and able to return for all scheduled follow-up visits (toddler and infant cohort)Be willing to avoid consumption (ingestion and topical application) of herbal or other local traditional medications throughout the course of the study. Also, be willing to avoid the use of medications (for example those available for purchase at local pharmacies) except those provided by the trial team (unless in an emergency) (adult cohort)Have a parent who is willing to ensure they avoid consumption (ingestion and topical application) of herbal or other local traditional medications throughout the course of the study. Also, who is willing to ensure they avoid the use of medications (for example those available for purchase at local pharmacies) except those provided by the trial team (unless in an emergency) (toddler and infant cohort)Have a readily identifiable place of residence within a reasonable travelling distance of the clinical trial siteThis aims to ensure home visits for solicited AE can be undertaken reliably and that the participant is able to present to the trial site or be reviewed at their home in the event of other unsolicited health complaints. No specific geographical limits are set with this regard. Rather, such decisions will be made based on the judgement of senior members of the field team based on their detailed knowledge of local geography and transport links.Have a consistent means of telephone contact for the duration of trial participation (adult cohort)Have a parent with a consistent means of telephone contact for the duration of trial participation (toddler and infant cohort)A telephone on a closed user group (CUG) network with the field team will be provided to participants/parents to ensure they are able to contact the investigator team at any time day or night without the need for telephone credit.Have a site on one wrist that is judged to be suitable for MNP administrationAdult female cohort only: have a negative serum pregnancy test at screening (visit 0) and negative urine pregnancy test on the day of vaccination (visit 1)Adult female cohort only: employ an effective method of birth control for 2 months preceding and throughout the studyEffective methods of birth control are defined as follows: credible history of continuous abstinence from heterosexual activity as a normal lifestyle choice, hormonal contraceptives (oral, injectable, implant, patch and ring), barrier contraceptives (condom or diaphragm, with spermicide) and intrauterine device. When using contraceptives, participants must have been using their current contraceptive for the past 2 months to be eligible. Adult female participants with documented sterilization via tubal ligation or hysterectomy may be enrolled although for completeness all female participants will undergo pregnancy testing as outlined above. Participants will never be encouraged to start using contraception to allow them to be eligible to join the study.Toddler cohort only: have been parenterally vaccinated against measles and rubella at between 9 and 12 months of ageBe willing to avoid MRV administration for the duration of enrolment in the study, including in the case of a national MRV campaign in The Gambia (adult cohort)Have a parent who is willing to ensure they avoid MRV administration for the duration of enrolment in the study, including in the case of a national MRV campaign in The Gambia (toddler and infant cohort)All toddlers and infants in the study will receive an additional SC dose of an MRV so will not miss out. Adults are not routinely included in MRV campaigns but will be given any missed doses under these circumstances.Be willing to avoid all vaccines not given by the trial team for the duration of the study except for non-measles and rubella vaccines given in national campaignsHave a parent who is willing to ensure they avoid all vaccines not given by the trial team for the duration of the study except for non-measles and rubella vaccines given in national campaigns (toddler and infant cohort).

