### Participant timeline {13}

The participant timeline is shown in Table 1.

**Table 1 Tab1:** Participant timeline

Visit #	V0	V1	Home visits	V2	V3	V4	V5
Study day	−14 to −1	0	1 to 13	7	14	42	180
Visit window (days)	-	-	-	+2	+3	+14	+28
Written informed consent	X						
History and physical examination	X	X		X	X	X	X
Vital signs and anthropometry	X	X		X	X	X	X
Screening and safety labs	X			X	X^a^		
Serum pregnancy test^b^	X						
Urinary pregnancy test^b^		X					X
Malaria rapid diagnostic test/blood film	X	X					
Immunogenicity blood samples	X					X	X
Final confirmation of eligibility		X					
Randomization and study product administration		X					
Solicited local and systemic AE data collection		X	X	X	X		
Unsolicited AE collection		X	X	X	X	X	X
EPI vaccine administration^c^						X	
T-cell responses — exploratory	X			X		X	X
Participant/parent experience — exploratory		X X^d^			X	X	
End of study							X‖

^a^Adult cohort only; ^b^adult females only; ^c^toddlers and infants will be administered the other EPI vaccines due at 15 to 18 months and 9 to 10 months/12 months respectively at V4 (day 42);^d^pre-vaccination (may also be conducted at V0) and post-vaccination; ‖toddlers and infants will be administered an additional SC dose of a measles and rubella vaccine on or after the end of study visit outside the current protocol to ensure protection based on the current EPI schedule in The Gambia

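### All toddlers and infants receive other EPI vaccines at day 42, inside the undivided day 0 to 180 unsolicited-AE outcome, so its all-cause counts mix in reactions to non-study vaccines; the sections also differ on which vaccines these are

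*Protocol article*

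**What the plan says.** Under Outcomes {12}, the second primary safety outcome is the "number, severity and relatedness of unsolicited AE and SAE from the day of study product administration until day 180". Trial design {8} gives the same span: "Unsolicited AE and serious adverse events (SAEs) will be collected from the day of study product administration to day 180 post-study product administration". Neither divides the period. Objectives {7} also carries the primary safety objective through to 180 days.

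The section on concomitant care {11d} places other vaccines inside that span. For infants it names "Other EPI vaccines due at 9 months in infants (yellow fever and bivalent oral poliovirus vaccine (bOPV"; for toddlers, "diphtheria, tetanus and pertussis and bOPV) will be administered at the day 42 post-vaccination visit". Table 1 confirms EPI vaccination at V4, and its footnote c reads "toddlers and infants will be administered the other EPI vaccines due at 15 to 18 months and 9 to 10 months/12 months respectively at V4". The window row, "Visit window (days) - - - +2 +3 +14 +28", allows V4 up to 14 days late and the final visit up to 28 days late.

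The AE definition in {18a} counts any untoward occurrence, related or not. Any AE not captured as solicited becomes an unsolicited AE. Solicited collection stops at day 13.

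**The concern.** After day 13, fever, irritability or a swollen injection site can be recorded only as an unsolicited AE. When such an event follows a vaccine given at V4, it enters the same primary count as an event after the study product. The statistical methods section {20a} says outcomes are tabulated by cohort and group and mentions no split by period. Section {20b} plans no additional analyses.

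The trial aims to describe whether the safety profile by patch is comparable to that by SC injection, in support of go/no-go decisions. A count that carries reactions to other vaccines describes the patch less well, and a difference between arms is harder to see in it.

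The second issue is textual. Three places describe the EPI vaccines deferred to day 42, and they do not match.

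**Working it through.** **The plan's own figure.** Table 2 gives 95.4% for at least one event with n = 60 and a true rate of 5%: 1 − 0.95^60 = 95.4%, reproduced. This figure is not in dispute. It is part of the design basis for the paediatric cohorts and refers to events in vaccinated children, with no allowance for events from other vaccines.

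**Who is affected.** From Trial design {8}: 120 toddlers + 120 infants = 240 of 45 + 120 + 120 = 285 participants (84%). Of the 150 MRV-MNP recipients, 60 + 60 = 120 are affected.

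**How much of the window follows V4.**
- V4 at day 42: (180 − 42)/180 = 138/180 = 76.7%.
- V4 at day 56: (180 − 56)/180 = 124/180 = 68.9%.
- Final visit at day 208: (208 − 56)/208 = 73.1% to (208 − 42)/208 = 79.8%.

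These are calendar shares. They do not measure how long vaccine reactions last.

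**Dilution.** Let a and b be the proportions with an unsolicited AE before V4 in the MNP and SC arms. Let e be the proportion with one from V4 onward, taken as equal in both arms and independent of the earlier events. The proportion with any event to day 180 is 1 − (1 − a)(1 − e) in the MNP arm and 1 − (1 − b)(1 − e) in the SC arm. The difference is (a − b)(1 − e).

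The documents give none of these rates. Assume a = 15%, b = 5%, 60 per arm, and e from 0 to 40%. The half-width is 1.96 × √[p₁(1 − p₁)/60 + p₂(1 − p₂)/60].

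| e | MNP | SC | Difference (points) | Ratio | 95% half-width (points) |
|---|---|---|---|---|---|
| 0 (period ends before the V4 vaccines) | 15.0% | 5.0% | 10.0 | 3.0 | 10.6 |
| 5% | 19.3% | 9.8% | 9.5 | 1.97 | 12.5 |
| 10% | 23.5% | 14.5% | 9.0 | 1.62 | 13.9 |
| 20% | 32.0% | 24.0% | 8.0 | 1.33 | 16.0 |
| 40% | 49.0% | 43.0% | 6.0 | 1.14 | 17.8 |

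In the MNP arm, the extra children counted per 60 are 60 × (p₁ − 0.15): 2.6 at e = 5% and 20.4 at e = 40%.

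**Event counts behave differently.** If both arms gain the same mean number of events per child, say 0.30 added to 0.20 and 0.10, the totals are 0.50 and 0.40. The difference stays at 0.10 and only the ratio moves, from 2.0 to 1.25.

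**The vaccine lists side by side.**
- {11d}: for infants, only vaccines due at 9 months (yellow fever, bOPV); for toddlers, diphtheria-tetanus-pertussis and bOPV.
- Known potential risks, on the delay to day 42: "yellow fever, poliovirus type 1 and 3 and meningococcus group A, diphtheria, tetanus and pertussis". Meningococcus group A is here but not in {11d}.
- Table 1 footnote c: for infants, vaccines due at 9 to 10 months/12 months, a wider span than {11d}.
- The bars on other vaccination also differ. The inclusion criteria ask participants or parents to "avoid all vaccines not given by the trial team for the duration of the study" and except only national campaigns. The exclusion criteria and {11d} also except catch-up vaccination. Read literally, the exclusion of planned vaccination during participation would cover the V4 vaccines themselves.

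**The case against.** Several objections have force.

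- **Relatedness is already part of the outcome.** The causality section has a clinician weigh timing, other explanations and concomitant medication, and class an event as not related when another cause is more likely. This separates many V4 reactions. It leaves the all-cause number and severity untouched, however, and does not name the EPI vaccines as an alternative cause.
- **Splitting tables is ordinary SAP work.** The SAP is not shown and may do it. But the outcome as stated is undivided, and nothing in the article signals a split.
- **No decision rule is distorted.** There is no hypothesis test or comparability margin. Solicited AEs, safety laboratories and the planned day-14 DMC reviews all precede V4. This is right, and it limits the weight of the point.
- **Intercurrent illness dilutes any long follow-up in the same way.** True, and e above would include it. The V4 vaccines differ in being a scheduled exposure at a known date, so they can be separated.

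A reader might go further and infer three things that the documents do not support. First, that the design is biased towards one arm: both randomized, blinded arms receive the same vaccines, so the effect is dilution. Second, that the protocol will report a pooled safety rate in 150 recipients mixing adults with vaccinated children: the n = 150 figures are sample-size illustrations, and results are tabulated by cohort and group. Third, that a child would go without meningococcus A vaccine until after day 180: the risk-section parenthesis explains why delay is acceptable and is not an administration schedule, and footnote c or the catch-up allowance may cover that vaccine.

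**Conclusion.** The point holds as a matter of dilution and of inflated single-arm, all-cause rates for unsolicited AEs in toddlers and infants. Adults are unaffected.

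That the exposure falls inside the outcome window is certain from the text. The size of the effect is not: it depends on e, which the documents do not give. The proportion-based difference shrinks by 1 − e, which is small at e = 5% and substantial at 40%. The illustration also assumes equal and independent V4-period events in the two arms and a product effect that shows before V4. On mean event counts the absolute difference is unchanged.

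The mismatch between vaccine lists is real but modest. Which list is right is for the sponsor to settle.

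**What to change.** Keep collection and the primary outcome to day 180, so that Outcomes {12} stays consistent with Objectives {7}. Add to {12} that, for toddlers and infants, unsolicited AEs are tabulated by arm for two periods: day 0 to V4 before the EPI vaccines are given, and V4 to day 180. State that the MNP versus SC comparison is read first from the earlier period, and that SAEs are reported over the whole period.

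Reconcile Known potential risks, {11d} and Table 1 footnote c on which EPI vaccines are given at V4. Align the bars on other vaccination in the inclusion criteria, the exclusion criteria and {11d} with that statement.

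The cost is a sentence in the outcomes, one split table using V4 dates already collected, and consistent wording across these sections. The first period will vary between 42 and 56 days because of the visit window. No data are lost.
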